### Monitoring, safety, and quality control

During the follow-up period, paper case report forms will be used to collect data. All data collection will be monitored in strict accordance with the standard procedures of the clinical trial center to ensure full compliance with International Coordinating Council standards and Good Clinical Practice principles. Any adverse events that occur in patients during the study period, such as worsening of clinical symptoms or loss of daily activity, will be fully evaluated through a doctor’s inquiry, physical examination, and imaging studies, and if adverse events are considered to be caused by intervention measures, the study will be discontinued and the patient will be treated symptomatically. Relevant data about the adverse events and the intervention measures in this study will be analyzed to improve the research measures. All adverse events will also be reported to the investigators. Due to short study period and low risk, we will not set up a trial steering committee. Any unexpected event will be reported directly to the investigator for comment. There is no interim analysis in this protocol, and [name] has the right to make the final decision on whether to terminate the trial.

Other treatment methods allowed in the control and experimental groups are as follows. (1) Both groups of patients can receive routine nursing treatment in the Second Spine Department of Xinjiang Uygur Autonomous Region Hospital of Traditional Chinese Medicine, including daily inquiries about the patient’s condition, pain improvement, and patient care. All nursing programs will be performed by the designated nurses of the Second Spine Department. (2) The acupuncture treatment for patients in the two groups after OLIF will be performed by the designated physician of the acupuncture department of the hospital. Additionally, the lumbar standardized acupuncture treatment is adopted, that is, all subjects have the same acupuncture treatment. (3) Traditional Chinese medicine treatment is also allowed as adjuvant therapy, and the patients in both groups receive the same treatment. Therefore, an effect of the above treatment on the overall trial results can be avoided. Other treatment methods prohibited for the control and experimental groups are as follows. (1) It is prohibited to perform other invasive treatments on the lumbar spine. (2) Subjects are prohibited from taking medications that can improve the related clinical symptoms. (3) No additional treatment may be given to patients included in the study without the consent of the investigator.

[name], a physician of Second Spine Department, had an informed conversation with each subject 2 days before surgery, and all subjects signed the informed consent form. After [name] obtained the informed consent of each subject, [name] from the Second Spine Department obtained from each subject the basic information and relevant medical history required for the trial, which was completed 2 days before surgery. [name], a physician of the Second Spine Department, checked whether the subjects met the prescribed inclusion criteria on the day before surgery and finally determined whether they were included in the trial. After [name] and [name] completed their work, investigator [name] assessed the VAS and ODI scores 1 day before surgery. The OLIF surgery in this study was performed by [name], the chief physician of the Second Spine Department, the Fourth Clinical Medical College of Xinjiang Medical University, according to the requirements of this study. Later, the follow-up data of the ODI, VAS, and BFS scores were collected by [name] and [name]. Importantly, for the same subject, the data should always be tracked and collected by the same person and cannot be performed alternately. Follow-up data collection should be completed within 24 h of the specified date. [name] is responsible for sorting and entering the collected data into the specified data acquisition form and setting the password for independent storage. This work is completed within 24 h of receiving the data.

### Dropout or loss to follow-up

All patients have the right to withdraw from the study at any time. If a patient chooses to withdraw from the study, we will revoke the patient’s consent and terminate the study participation. The chief investigator may also terminate a subject’s participation if the subject violates the rules of management for this study or has a serious adverse event. Data of these subjects will be excluded in the final analysis.

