### Randomization and blinding

Physicians [name] and [name], from the Fourth Affiliated Hospital of Xinjiang Medical University, will use computer software to generate random sequences, which will be sealed in envelopes. Eligible patients will be recruited by physicians of the department, [name] and [name]. The recruited patients will be randomized into two groups by [name], a physician of the department. In order to avoid the predictability of random sequences, the envelopes used are all of the same kind of envelope produced by the same manufacturer (that is, the appearance, thickness, texture are the same), and all sequences are not disclosed to recruiters and allocations. In this study, a single-blind approach will be adopted, that is, participants do not know which treatment they are receiving. The specific procedures performed will be kept confidential to all participants until unblinded.

To ensure the scientific accuracy of the study, it is also planned to charge the same fee for all subjects. The specific charges are as follows: preoperative preparation fee, surgery fee, anesthesia fee, cost of related equipment used during operation, and cost of intraoperative and postoperative drugs. In particular, the spinal orthoses used by the patients in the experimental group will be uniformly distributed by the research team to ensure that the spinal orthoses used by the patients in the experimental group are the same; thus, the cost of spinal orthoses will not be included. The total cost is RMB 55969.32.

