### Statistical analysis

The Epidtat3.0 software is adopted to enter the observation data by two members of the research group alone, and SPSS18.0 is applied for statistical analysis. Demographic and clinical characteristics (such as gender, age, and weight) of all subjects will be processed based on descriptive analysis. Quantitative data will be expressed as the mean, standard deviation, median, and range and qualitative data will be presented as frequencies and percentages. Chi-square test will be used to compare the incidence of related adverse events between the two groups.

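### Excluding withdrawn and terminated patients from the final analysis can bias the randomised comparison and remove serious adverse events from the safety test

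*Protocol article*

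**What the plan says.** The section Dropout or loss to follow-up covers two routes out of the trial. The first is the patient's own choice: "If a patient chooses to withdraw from the study, we will revoke the patient’s consent and terminate the study participation." The second is a decision by the investigator: "The chief investigator may also terminate a subject’s participation", on the grounds "if the subject violates the rules of management for this study or has a serious adverse event". The paragraph closes with: "Data of these subjects will be excluded in the final analysis." It makes no exception for safety data or for data collected before the patient left.

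Three other places bear on this:

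- Statistical analysis names one between-group test: "Chi-square test will be used to compare the incidence of related adverse events between the two groups." It does not say whether excluded patients count. Its reference to all subjects concerns descriptive baseline characteristics only.
- Monitoring, safety, and quality control says that data on adverse events will be analysed, in order to improve the research measures, and that all such events go to the investigators. It also says that "if adverse events are considered to be caused by intervention measures, the study will be discontinued and the patient will be treated symptomatically".
- Randomization and blinding says "a single-blind approach will be adopted, that is, participants do not know which treatment they are receiving". It does not say that the chief investigator is unaware of allocation.

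The article contains no as-randomised analysis statement and no separate safety population.

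**The concern.** Randomisation makes the two groups comparable at the start. Removing patients for what happens afterwards keeps that comparability only if removal is unrelated to outcome or acts alike in both arms. The stated grounds give no such assurance. A serious adverse event is itself a poor outcome. Withdrawal may follow a poor result. Termination is a judgement by someone who may know the allocation.

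Some grounds are specific to one arm. Group A alone is assigned a wearing schedule (end of the OLIF surgical technique section), and the Background lists skin irritation and muscle atrophy as possible effects of orthoses worn improperly or not for the prescribed time. Failure to wear the orthosis and harms from it can therefore arise only in group A. Withdrawal, prohibited treatment and surgical events can arise in either arm.

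Two things are at stake. One is whether the difference in ODI, VAS and fusion score still compares the groups as randomised. The other is whether the adverse-event comparison, the only between-group test the article names, includes the events that matter most.

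**Working it through.** **Inputs from the Sample size section.** α = 0.05, D = 0.64, δ² = 0.46, selected row of Table 1 with β = 0.1 and Δ = 0.2, 20% dropout, 30 patients per group.

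**The plan's own figure.** n = 2(Zα + Zβ)²δ²/(D − Δ)² = 2 × (1.960 + 1.282)² × 0.46/0.44² = 49.93, so 50. This matches Table 1 and shows that α is two-sided. The SD used below is √0.46 = 0.678. The expression printed for δ² evaluates to 0.449 (SD 0.67); using it would change the shifts below by less than 0.003.

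**Efficacy.** Assume a normal outcome, no true effect, and exclusion of a fraction p of an arm driven by a normal tendency that correlates ρ with poor outcome. The arm's mean then shifts by ρ × SD × φ(z₁₋p)/(1 − p).

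- p = 20%: φ(0.842)/0.80 = 0.280/0.80 = 0.350 SD, × 0.678 = 0.237.
- p = 5%: φ(1.645)/0.95 = 0.103/0.95 = 0.109 SD, × 0.678 = 0.074.

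| Excluded, one arm vs other | ρ = 0 | ρ = 0.3 | ρ = 0.5 | ρ = 1 (worst always removed) |
|---|---|---|---|---|
| 20% vs 20% | 0 | 0 | 0 | 0 |
| 20% vs 5% | 0 | 0.05 | 0.08 | 0.16 |
| 20% vs 0% | 0 | 0.07 | 0.12 | 0.24 |

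Only the bottom-right cell exceeds the margin of 0.2; it is 0.237/0.64 = 37% of D. The values of ρ and the split between arms are assumptions. The plan's 20% is an overall allowance, not a rate for one arm.

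**Precision.** Excluding 20% of 30 leaves 24 per arm. Power = Φ(0.44/√(2 × 0.46/n) − 1.96). For n = 30 this is Φ(2.513 − 1.96) = 71%; for n = 24 it is Φ(2.247 − 1.96) = 61%. The 71% is a ceiling, because it needs outcomes on all 60 patients. Both figures lie below the planned 90% because the formula's 50 is a number per group, whereas the plan treats it as a total; that is a separate matter.

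**Safety.** Assume 6/30 patients with a serious adverse event in one arm and 1/30 in the other.

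- All counted: uncorrected χ² = 60 × (6 × 29 − 24 × 1)²/(7 × 53 × 30 × 30) = 4.04, p = 0.044 (Fisher's exact p = 0.103).
- Three of the six terminated and excluded: 3/27 vs 1/30, χ² = 57 × (3 × 29 − 24 × 1)²/(4 × 53 × 27 × 30) = 1.32, p = 0.25.
- All seven terminated and excluded: 0/24 vs 0/29, with nothing left to test.

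The counts are invented. The example shows only that the loss grows with how often the rule is used.

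**The case against.** The strongest reply is that the rule is narrower than it looks and its effect is unknown. Much of that stands.

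- **Termination is discretionary.** A reader might infer that every patient with a serious adverse event or a rule breach is deleted. The text says the investigator may terminate; exclusion follows only if that happens. Removal is possible, not automatic.
- **The bias is not one-sided by design.** A reader might infer this from the orthosis-specific grounds. All patients have the same operation, and the treatment prohibitions apply to both groups. The net direction cannot be read from the document.
- **Symptom-relieving medication does not clearly lead to deletion.** The protocol does state "Subjects are prohibited from taking medications that can improve the related clinical symptoms", and a patient in pain is a likely person to breach that. But the dropout section never defines the rules it refers to, nothing ties them to this prohibition, and additional treatment is possible with the investigator's consent. The link is an inference.
- **Adverse-event data are said to be analysed.** This appears under monitoring, so the document does not plainly discard them. But the purpose given there is improving the research measures, and no safety set is defined. The monitoring, dropout and statistical sections remain unreconciled.
- **Outcome evaluators and analysts are separate from grouping.** Methods/design says so. That does not cover the decision to terminate.
- **Withdrawn consent may require removal of data.** It may, and the fix allows for it. Patients terminated by the investigator have not withdrawn consent.

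Nor is this a gap for an unseen analysis plan to fill. The exclusion is stated outright, and an analysis plan that kept everyone in would contradict it.

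**Conclusion.** The point holds as a stated rule that can bias the efficacy comparison and that removes serious adverse events from the safety comparison wherever it is applied to them. Confidence is high that the rule exists and that nothing in the article offsets it. It is low on the direction and size of any efficacy bias.

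Under the assumptions shown, the shift runs from zero, through 0.07 to 0.12 for a moderate link with outcome at 20% vs 0% exclusion, to at most 0.24. A reader might take 0.24 as the expected bias. It is an upper bound, requiring that only the worst patients of one arm be removed and none of the other. The unit is also unknown, since the Sample size section mentions ODI, VAS and NRS without saying which scale D is on. The case for change rests on the rule itself, not on that figure.

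**What to change.** Replace the exclusion sentence in Dropout or loss to follow-up with:

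> All randomised patients are analysed in the group to which they were assigned, using all data collected, including data collected before withdrawal or termination, unless the patient withdraws consent for use of those data. Adverse events, including those that led to termination, are counted in all randomised patients.

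Keep the exclusion-based set only as a per-protocol sensitivity analysis. Reconcile the monitoring, dropout and statistical sections, so that it is clear which patients and events enter the chi-square test. The handling of patients with no later outcome can be left to the analysis plan. The rules for terminating participation stay as they are; the change concerns only the analysis population and the retention of data.

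The cost is one paragraph of protocol text and a small change to the consent wording on retained data, which may need ethics approval because the protocol now treats withdrawal as revoking consent. The estimated effect may be somewhat diluted by patients who left the assigned regimen. No extra patients are needed. The article gives April 2023 as the recruitment date, so the change should be dated and made before the final analysis.

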### Main result measurement

A variety of outcome measures are used in this study, including the VAS (0–10 points) and ODI (0–50%), and are evaluated 1 day before surgery and 1, 3, and 6 months and 1 year after surgery. The ODI is used to assess disability associated with low back pain. The ODI has 10 questions about daily activities, including pain intensity, personal care, weight lifting, walking, sitting, standing, sleeping, sex, social life, and travel, each of which is rated on a scale of 0 to 5 points. The lower the score, the less affected the person is by pain. The VAS uses 0 points to indicate no pain and 10 points to indicate the peak of pain within the patient’s perception range, and the VAS is a self-assessment tool for pain consisting of 0 and 10 at either end of a straight line. Participants mark a point on the line to indicate their average pain level. The above two scales have been recognized by the medical community, and the value and effectiveness of the VAS and ODI scales have been demonstrated by related studies [30, 31]. The BSF score ranges from 0 to 4, where 0 points indicate no connection between the upper and lower parts of the vertebral body, height loss, and bone grafting absorption and 4 points indicate complete fusion and good shaping. The higher the score, the greater the degree of fusion. The main outcome measures in this study are the ODI, VAS, and BFS scores after follow-up and efficacy evaluation obtained as required. The above scores will be obtained by the designated personnel through follow-up visit. After obtaining the scores of the two, the efficacy is evaluated according to Table 4. Because the final efficacy evaluation of each patient is significantly affected by the above scores, which indirectly plays a decisive role in the results of the study, the relevant data should be obtained in strict accordance with the requirements during the follow-up process. The specific efficacy evaluation criteria are stated in Table 5.

**Table 5 Tab5:** Efficacy evaluation

	Efficacy			
	Cured	Significantly effective	Taking effect	Ineffective
Evaluation index				
ODI score	≤ 40%	40–59%	60–70%	> 70%
VAS score	< 2	2–3	4–5	> 5
BSF score	≥ 3	2	1	0

*VAS*, visual analog scale; *ODI*, Oswestry disability index; *BFS*, Brantigan, Steffee, Fraser

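### Excluding the data of patients terminated for a serious adverse event can remove from the safety comparison the events it is meant to count, and breaks analysis as randomised

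*Protocol article*

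**What the plan says.** The rule is in the protocol article, section Dropout or loss to follow-up. Patients may withdraw at any time, in which case the team will revoke the patient's "consent and terminate the study participation". The chief investigator may also end participation if the patient "violates the rules of management for this study or has a serious adverse event". The paragraph closes with "Data of these subjects will be excluded in the final analysis". It makes no exception for safety data.

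The section Statistical analysis gives the only planned between-group safety comparison: "Chi-square test will be used to compare the incidence of related adverse events between the two groups". It names no population for that test.

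The section Monitoring, safety, and quality control says "All adverse events will also be reported to the investigators" and "Relevant data about the adverse events and the intervention measures in this study will be analyzed to improve the research measures". Its examples of adverse events are "such as worsening of clinical symptoms or loss of daily activity". It also provides for discontinuation when an event is judged to be caused by the intervention.

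**The concern.** The reason for exclusion arises after randomisation and is itself an outcome. A serious adverse event is something the safety comparison should count, yet it can take the patient out of both numerator and denominator.

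The efficacy comparison is exposed to the same selection. The article's examples of adverse events are worsening symptoms and lost activity, which lie close to what VAS and ODI measure; of the latter the section Main result measurement says "The ODI is used to assess disability associated with low back pain". If patients who do badly leave the analysis, the arm that loses more of them looks safer and more effective than it was.

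The document does not settle the direction. Both groups have the same surgery, so either can have such events.

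**Working it through.** **Reading the sections together**

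1. Who is excluded? At the least, patients terminated for a serious adverse event or a rule violation. Withdrawals come earlier in the same paragraph, so the natural reading covers them too.
2. Is exclusion automatic after a serious event? No. The chief investigator may terminate but need not, so the event is lost only when termination follows.
3. Does another section put these patients back? Reporting events to investigators, and analysing them in order to improve the research measures, is not a comparison between groups. The statistical section's reference to all subjects concerns demographic and clinical characteristics only. Nothing in the article overrides the exclusion.

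**Inputs**

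- From the section Sample size and its Table 1: 30 patients per group, D = 0.64, variance 0.46, superiority bound 0.2, dropout allowance 20%.
- Assumed, because the document gives no figures: event counts, exit fractions, and the correlation between exit and outcome.

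The planning inputs reproduce the plan's own figure. With two-sided α = 0.05 and β = 0.1, n = 2(1.960 + 1.282)² × 0.46 / (0.64 − 0.2)² = 49.93, rounded up to the 50 in Table 1. The SD used below is √0.46 = 0.678.

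**Safety illustration: three related events among 30 patients in one group**

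| Patients with an event who are terminated and excluded | Analysed rate |
|---|---|
| 0 | 3/30 = 10.0% |
| 1 | 2/29 = 6.9% |
| 2 | 1/28 = 3.6% |
| 3 (worst case) | 0/27 = 0% |

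Against 0/30 in the other group, the uncorrected chi-square test on the full data gives p = 0.076. It is not significant even with nothing excluded, so the harm in this example is to the reported rate.

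With more events the test can change as well. For 6/30 against 1/30 the uncorrected p is 0.044. If three of the six patients are excluded, the comparison becomes 3/27 against 1/30 and p = 0.25. With continuity correction the values are 0.108 and 0.53, so this change of conclusion depends on using the uncorrected test.

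**Efficacy illustration: upper bound**

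Assume a normal outcome, with exactly the worst fraction p of one arm removed and the other arm intact. The shift in that arm's mean is SD × φ(z)/(1 − p), with z = Φ⁻¹(1 − p).

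| p | φ(z) | Shift | Share of D = 0.64 | Shift if exit correlates 0.5 with outcome |
|---|---|---|---|---|
| 5% | 0.103 | 0.678 × 0.103/0.95 = 0.074 | 12% | 0.037 |
| 10% | 0.175 | 0.678 × 0.175/0.90 = 0.132 | 21% | 0.066 |
| 20% | 0.280 | 0.678 × 0.280/0.80 = 0.237 | 37% | 0.119 |

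A simulation with 30 patients per arm gives 0.126 when the worst three are removed and 0.229 when the worst six are, in line with the 10% and 20% rows. The 20% row exceeds the superiority bound of 0.2, but it needs an arm's whole dropout allowance to be outcome-related.

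**The case against.** The strongest objections concern reach and size.

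- **Narrow overlap.** The test counts related events; the termination clause concerns serious ones and is discretionary. Through that clause, only events that are serious, related and followed by termination are lost. This stands as a limit on size. It does not remove the fault, and the provision to discontinue after an intervention-caused event makes termination for related events more plausible, although the article does not say whether that provision triggers the exclusion.
- **Efficacy link inferred.** Worsening symptoms and lost activity are given as examples of adverse events in general, and the article does not call them serious. Selection on VAS or ODI is therefore possible but not shown. This stands.
- **Efficacy figures idealised.** They assume one-sided loss of exactly the worst patients, and the sample size section does not say which scale its SD and difference belong to. This stands. They are upper bounds in planning units and cannot be placed on ODI, VAS or BSF.
- **A fuller document may define a safety population.** The article is condensed, and final analysis might mean only the efficacy analysis. But the article states an exclusion rule in general terms. A safety or intention-to-treat population defined elsewhere would contradict that rule, so the wording needs correcting either way.
- **Withdrawn consent may bar use of earlier data.** This is fair, and the fix allows for it.

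**Conclusion.** The concern holds. The article states a rule that, if followed, can drop from the adverse-event comparison the patients whose events it should count, and that departs from analysis as randomised for efficacy.

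The fault in the text is definite. Its size and direction in this trial are unknown, because no event or exit rates are given. With 30 patients per group, two or three exclusions are enough to change a reported event rate materially. For efficacy, the bias could reach 12% to 37% of the planned difference under the extreme assumption of one-sided loss of the worst 5% to 20%. It would be about half that if exit correlates 0.5 with outcome, and close to zero if both arms lose similar patients at similar rates. The rule should be changed.

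**What to change.** - **Dropout or loss to follow-up:** replace the exclusion with analysis of all randomised patients by assigned group, using data collected up to exit. For withdrawals, use them as far as consent allows. Continue the planned visits for patients who stop the orthosis or are terminated, where they agree.
- **Statistical analysis:** count every adverse event in every randomised patient, with the number randomised per group as denominator. Keep a per-protocol analysis as secondary.

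The cost is wording in two sections, plus follow-up at visits already scheduled for the few terminated patients who agree to it. The drawback is some dilution of the estimated effect of wearing the orthosis as prescribed, which the secondary per-protocol analysis can show.

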## Abstract

**Background:**

Oblique lumbar interbody fusion (OLIF) is an internationally popular minimally invasive technology for the treatment of various lumbar diseases. Since its introduction to China in 2014, OLIF technology has clearly shown its superiority in reconstructing intervertebral stability, restoring intervertebral space height, achieving indirect decompression, and restoring normal lumbar sequence. However, some patients still suffer from persistent symptoms after OLIF, including low back pain and soreness, which indirectly affect the overall surgical efficacy and patient satisfaction. Therefore, some clinicians recommend that patients routinely use spinal orthoses after OLIF to reduce the stress on the lower back muscles and ligaments, thereby relieving or avoiding postoperative residual symptoms or new symptoms. Accordingly, spinal orthosis use after OLIF has emerged as an essential option. However, the role of spinal orthoses in OLIF and their specific impact on postoperative patient clinical outcomes have remained unclear, and there is a lack of strong clinical evidence to indirectly or directly support the role of spinal orthoses in OLIF and demonstrate their impact on patient clinical outcomes. This study aims to investigate the role of spinal orthoses in OLIF by grouping patients based on the use or nonuse of spinal orthosis after OLIF, thus providing a better basis for the majority of patients and physicians.

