It is well established that any type of surgery is a form of trauma for human beings, regardless of the size of the trauma, but it is also likely to cause damage, and some such damage is even harmful. Despite many advantages of OLIF in lumbar spine surgery, it is also an invasive operation for the body, which may lead to residual symptoms or new complications in some patients after surgery and may indirectly increase the rate of lumbar reoperation and reduce the effect of surgery [18]. Therefore, it is imperative to adopt other means after lumbar surgery to reduce residual symptoms and postoperative complications. The commonly used clinical approaches include prolonged bed rest after surgery, avoidance of labor, lifting heavy articles, and prolonged standing or sitting and wearing a spinal orthosis. A better and commonly used clinical method to avoid reducing the quality of life of patients after surgery is to wear a spinal orthosis routinely after surgery.

Generally, fixation of any musculoskeletal injury is favorable for reducing the pain after injury [19]. Therefore, spinal orthoses can be used not only to relieve residual back pain symptoms [20] but also for postoperative rehabilitation of patients after lumbar spine surgery [21]. The use of spinal orthosis after OLIF is to fix the entire body movement [22] and the motion segment, relieve muscle strength [23], reduce pain [24], enhance the fusion rate [25], and improve the functional prognosis [26]. However, it is undeniable that non-standard or the wearing of spinal orthoses not for the prescribed time after surgery may also lead to muscle atrophy [27], skin irritation, delayed recovery, and other side effects.

For this reason, although the spinal orthosis exhibits some advantages after lumbar fusion, the necessity of its clinical use has been questioned due to its limitations. Additionally, the role of postoperative orthoses in OLIF has not been determined, and there is a lack of strong evidence to prove any correlation between the routine use of orthoses after OLIF and the final clinical outcome of patients. Therefore, we plan to conduct a randomized trial to evaluate the necessity of using lumbar orthoses after OLIF for postoperative adjuvant therapy in such patients.

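### Randomised patients who withdraw, are terminated for breaking study rules or have a serious adverse event lose all their data, for reasons that can depend on pain and disability

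*Protocol article*

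**What the plan says.** The section Dropout or loss to follow-up names three ways out of the trial. A patient may withdraw at any time. The chief investigator may end participation if "the subject violates the rules of management for this study", or if the patient has a serious adverse event. The section closes with: "Data of these subjects will be excluded in the final analysis". Read with the sentences before it, this covers all three groups.

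Other text bears on who might leave:

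- Monitoring, safety, and quality control lists treatments prohibited in both groups. Item 2 reads: "Subjects are prohibited from taking medications that can improve the related clinical symptoms". Item 3 reads: "No additional treatment may be given to patients included in the study without the consent of the investigator".
- The same section allows nursing care, standardised acupuncture and traditional Chinese medicine in both arms. For adverse events attributed to the intervention it says "the study will be discontinued and the patient will be treated symptomatically".
- Randomization and blinding includes "cost of intraoperative and postoperative drugs" among the charges, so some postoperative drugs are expected.
- Main result measurement makes ODI, VAS and the BSF fusion score the main outcomes.
- Statistical analysis names no analysis population.

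**The concern.** Randomisation makes the two arms comparable at the start. Dropping patients later for a reason linked to the outcome can undo that, and all three exclusion grounds can be linked to it.

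- **Withdrawal.** A patient who is doing badly may be more inclined to leave.
- **Serious adverse event.** The article's own examples of adverse events are worsening symptoms and lost daily function, which is close to what VAS and ODI record. Not every such event would be serious.
- **Rule violation.** If the medication ban is one of the rules, the patient likeliest to break it is the one in most pain. The abstract expects that "some patients still suffer from persistent symptoms after OLIF, including low back pain and soreness".

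The termination decision is discretionary. The article blinds participants, and it separates outcome evaluation and analysis from grouping. It states no blinding for the person who decides on termination.

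At stake is the VAS and ODI comparison in a trial of 30 patients per arm, where a few exclusions can matter. The fusion score is less exposed.

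**Working it through.** **Step 1. Is the rule fixed, and does anything override it?** The exclusion sentence is an affirmative rule, not a detail left for an analysis plan. The Statistical analysis section gives no population that would keep these patients in, and no section keeps data collected before termination. The permitted treatments and postoperative drugs may make violations rarer. None of that text says that a patient who withdraws or is terminated stays in the analysis.

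**Step 2. What does the document give on size?** It gives no exclusion rates by arm and no link between exclusion and pain. The Sample size section supplies only a scale to work on: a difference D = 2.09 − 1.45 = 0.64, a variance of 0.46, a 20% dropout allowance and 30 patients per arm. It does not name the outcome scale. Its selected row reproduces with two-sided α = 0.05, β = 0.1 and bound 0.2:

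n = 2(1.960 + 1.282)² × 0.46 / (0.64 − 0.2)² = 49.9, rounded up to 50.

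The SD is √0.46 = 0.678, so 0.64 is 0.94 SD.

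**Step 3. Illustration A: exclusions in one arm only.** The assumptions, none of them in the document, are that k of 30 patients are excluded in one arm and none in the other. The excluded patients are those ranking highest on a variable with correlation r to pain. That arm's mean then falls by

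r × (sum of the k largest expected normal order statistics of 30) / (30 − k), in SD units.

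For k = 1 and r = 1 this is 2.04 / 29 = 0.070 SD, or 0.070 × 0.678 = 0.048 units. The value k = 6 is 20% of 30.

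| k | Sum | r | Fall (SD) | Fall (units) | Difference, controls only excluded | Difference, orthosis only excluded |
|---|---|---|---|---|---|---|
| 1 | 2.04 | 0.5 | 0.035 | 0.024 | 0.62 | 0.66 |
| 3 | 5.02 | 0.5 | 0.093 | 0.063 | 0.58 | 0.70 |
| 6 | 8.12 | 0.5 | 0.169 | 0.115 | 0.53 | 0.75 |
| 1 | 2.04 | 1 | 0.070 | 0.048 | 0.59 | 0.69 |
| 3 | 5.02 | 1 | 0.186 | 0.126 | 0.51 | 0.77 |
| 6 | 8.12 | 1 | 0.338 | 0.229 | 0.41 | 0.87 |

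The largest shift is 0.229 / 0.64 = 36% of the planned difference. With exclusions in both arms, 4 against 2, the net shift is 0.04 (r = 0.5) to 0.07 (r = 1), about 6 to 11% of 0.64. With equal exclusions the difference stays near 0.64.

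**Step 4. Illustration B: one rule, applied alike in both arms.** Assume normal scores with means 1.45 (orthosis) and 2.09 (control) and variance 0.46. Exclude a fraction q of patients above a threshold t.

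| t | q | Orthosis lost | Control lost | Difference |
|---|---|---|---|---|
| 2.5 | 25% | 1.5% | 6.9% | 0.60 |
| 2.5 | 100% | 6.1% | 27.3% | 0.42 |
| 3.0 | 25% | 0.3% | 2.2% | 0.62 |
| 3.0 | 100% | 1.1% | 9.0% | 0.54 |

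A common rule therefore need not remove patients equally; the arm with more pain loses more. The 0.42 row takes 27.3% of controls, more than the 20% allowance in that arm, although the loss over both arms is (27.3 + 6.1) / 2 = 16.7%.

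**The case against.** The strongest objection concerns the medication route. For a painkiller to cost a patient their data, four things must hold. The ban must be among the study rules, which the article leaves undefined. The drug must count as banned. The investigator must not have consented to it. The chief investigator must then choose to terminate. The article also condenses a fuller protocol that could define the rules, and it leaves patients several permitted routes to relief. All of this stands. A reader might infer that anyone who takes pain relief is automatically removed, and the text does not support that. Nor is the ban itself a fault: restricting co-treatment equally in both arms is a legitimate choice.

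The objection does not reach the explicit part of the rule. Withdrawals and serious adverse events lead to exclusion without any inference about medication.

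A second objection is that the sizes are assumed. That also stands. A reader might infer that the rule would manufacture an orthosis benefit, or wipe one out. The document supports neither. Under the trial's stated assumption that orthosis patients do better, more controls would be lost and a benefit would shrink. Inflation would need more losses in the orthosis arm. The Background section does mention "skin irritation, delayed recovery, and other side effects", but ties these to non-standard wear or not wearing the orthosis for the prescribed time, and does not connect them with withdrawal or analgesic use.

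**Conclusion.** The point holds for the exclusion rule as a whole. Followed as written, it removes randomised patients after randomisation for reasons that can depend on the VAS and ODI outcomes, and nothing shown overrides it. The medication ban is a plausible further route, but only if it counts as one of the rules and the chief investigator acts on it.

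Size and direction are unknown. In the one-arm illustration the planned 0.64 moves to between 0.41 and 0.87. Even the extreme case (6 exclusions against none, perfectly tied to pain) weakens the effect by about 36% and does not remove it. Milder or balanced exclusions shift it little. These figures rest wholly on assumed rates and correlations and on the Sample size section's unnamed scale. The change is worth making because the fault is explicit and the remedy is cheap.

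**What to change.** Replace the last sentence of Dropout or loss to follow-up with a rule to this effect:

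- Every randomised patient is analysed in the assigned group.
- Data collected before withdrawal or termination are kept where consent allows.
- Follow-up continues after a rule violation, including use of symptom-relieving medication, or after a serious adverse event, where the patient agrees.
- Any analysis that leaves these patients out is a per-protocol sensitivity analysis only.

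Exempting medication use alone would be too narrow, because withdrawals, serious adverse events and other violations would still be excluded.

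An optional addition is to record symptom-relieving medication at each visit and report it by arm beside VAS and ODI. This does not remove bias, but it shows whether use differed. It adds one case report form question, with some recall error.

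The cost is a short amendment, continued follow-up of some patients who would otherwise have left, and some dilution of the treatment contrast from medication use among patients who are kept. Trial status gives April 1, 2023 as the recruitment date, so the amendment may fall after recruitment has begun. It should be dated and made before the outcome data are analysed.
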